**2.3 Trial Entry**

The **second screening visit** (study visit 2) takes place one to four weeks before the first planned injection. A member of the study team will confirm that the volunteer is at low risk of HIV-1 infection, that all inclusion criteria are fulfilled (see section 1.3.1), that no exclusion criteria exist (see section 1.3.2) and the volunteer understands and agrees to the concept of practicing effective contraception. If not already done at the prior visit, the study doctor will take a complete medical history and perform a physical examination including mouth and throat inspection, palpation of lymph nodes, cardiac and pulmonary auscultation, abdominal palpation, blood pressure and body temperature. Medical status and medical history, including any ongoing medication and any previous allergic reactions, will be documented. The volunteer will again receive an extended information, both oral and in written, describing the study.

The volunteer will also be informed that s/he is free to end all obligations in the study whenever s/he wishes and that a premature ending will not have any negative influence in future contacts with the clinic. At this visit the study nurse confirms that the volunteer fulfils all the inclusion criteria, including laboratory results, makes an abbreviate risk assessment and a brief summary of the study design. Reassurance has to be made that the study subject fully understands the concept of the study. A mobile/telephone number and name of contact is obtained for the follow up. The results of the screening investigations will be reviewed and volunteers who are still eligible and willing will be asked to complete part 2 of the Informed consent. Blood is donated according to flow chart and an ECG evaluation will be performed.

The visit should be recorded in the source documents including conformity to inclusion and exclusion criteria, study number and any other information relevant to inclusion in the study.

2.4 Randomisation and study procedures

At **week 0 (study visit 3)** the study subject again meets both study nurse(s) and study doctor(s). Once again confirmation has to be made that the volunteer fulfils all inclusion criteria, including laboratory results, and fully understands the concept of the study. If no contraindications are revealed the study subject is randomised into one of the three study groups (B1 – B3) in the first part of the study and to group B4 in the second part of the study and again blood is donated for safety laboratory tests. The randomisation procedure is documented. The individuals can participate in the trial without consent to genetic analyses.

A randomization list comprising the 48 vaccination assignments will be prepared by an independent statistician in two sets, one of 36 (B1-3) and one of 12 (B4). Labels with the corresponding assignments will be placed in numbered two serials of envelopes (one for groups B1-3 and another for group B4) by the pharmacist and sealed. The randomization schedule will be kept under lock by the pharmacist and the envelopes delivered to the clinic. In case of drop-outs prior to the first immunization the labels will be returned to the pharmacist who will undertake a second randomization at the end of the recruitment. Drop-outs after the end of the recruitment will not be replaced. After randomization blood is donated according to flow chart and the first injection is given. The study visit is documented. Volunteers will be observed for 30 minutes following injection for acute adverse experiences and will also be contacted the day following injection by the study nurse for a brief adverse reaction interview. The number given for the follow-up telephone contact and the contact (in case the volunteer is not reached) is checked as current. In addition, volunteers will complete diaries over events for 7 days following each vaccination and receive telephone numbers to call, all hours of the day for 7 days after the vaccination, in order to get in contact with the clinic if needed. A folder with diary cards, thermometer and a ruler will be issued to each patient. The visit should be recorded in the source documents including immunization, study number and any other information relevant to the study.

**Week 2 (study visit 4)** is conducted by the study nurse(s). The study form is filled in and blood donated according to flow chart. Abbreviated risk assessment and risk behaviour counselling is done. The visit should be recorded in the source documents including study number and any other information relevant to the study.

**Week 6 (study visit 5),** the visit for the second injection of the study vaccine, is conducted by both the study nurse and the study doctor. Before injection the diaries on events after the last injection will be discussed with the study subjects and an abbreviated risk assessment and risk behaviour counselling will be performed. Enough time has to be planned for the visit so that all questions from the volunteer about the study can be answered or reflected upon. After blood donation the second injection is given and the visit is documented. Again volunteers will be observed for 30 minutes following injection and new diaries on events will be completed for 7 days. The visit should be recorded in the source documents including immunization, study number and any other information relevant to the study.

**Week 8 (study visit 6)** is conducted by the study nurse(s). The study form is filled in and blood donated according to flow chart. Abbreviated risk assessment and risk behaviour counselling are done. The visit should be recorded in the source documents including study number and any other information relevant to the study.

**Week 12 (study visit 7),** the visit for the third injection of the study vaccine, is conducted by both the study nurse and the study doctor. Before injection the diaries over events after the last injection will be discussed with the study subjects and an abbreviate risk assessment and risk behaviour counselling will be performed. Enough time has to be planned for the visit so that all questions from the volunteers about the study can be answered or reflected upon. After blood donation the third injection is given and the visit is documented. Again volunteers will be observed for 30 minutes following injection and new diaries over events will be completed for 7 days. The visit should be recorded in the source documents including immunization, study number and any other information relevant to the study.

**Study visits 8, 9 and 10** planned at weeks 14, 16 and 32 respectively. They are all conducted by the study nurse(s). At all visits the study forms are fulfilled and blood donated according to flow chart. Abbreviated risk assessment and risk behaviour counselling are planned for all visits except at visit 4 (two weeks after the last injection) when only blood tests and discussion over “event diaries”, fulfilled after the second injection, are planned. However at all time points enough time has to be planned in order to answer questions from the volunteers. Optionally at visit 8 or 9 a 3 mm punch biopsy will be taken from the site of the electroporated immunization site. At visit 10, eligibility for the next phase of immunization will again be checked.

**Week 36 (study visit 11)**, the visit for the forth injection of the study vaccine, is conducted by both the study nurse and the study doctor. Before injection the diaries over events after the last injection will be discussed with the study subjects and an abbreviate risk assessment and risk behaviour counselling will be performed. Enough time has to be planned for the visit so that all questions from the volunteers about the study can be answered or reflected upon. After blood donation the third injection is given and the visit is documented.

Again volunteers will be observed for 30 minutes following injection and new diaries over events will be completed for 7 days. The visit should be recorded in the source documents including immunization, study number and any other information relevant to the study.

**Week 38 (study visit 12)** is conducted by the study nurse(s). The study form is filled in and blood donated according to flow chart. Abbreviated risk assessment and risk behaviour counselling are done. The visit should be recorded in the source documents including study number and any other information relevant to the study.

**Week 40 (study visit 13)** is conducted by the study nurse(s). Blood is donated according to flow chart.

**Week 60 (study visit 14)** the visit for the fifth and last injection of the study vaccine, is conducted by both the study nurse and the study doctor. Before injection the diaries over events after the last injection will be discussed with the study subjects and an abbreviate risk assessment and risk behaviour counselling will be performed. Enough time has to be planned for the visit so that all questions from the volunteers about the study can be answered or reflected upon. After blood donation the fifth injection is given and the visit is documented. Again volunteers will be observed for 30 minutes following injection and new diaries over events will be completed for 7 days. The visit should be recorded in the source documents including immunization, study number and any other information relevant to the study.

**Week 62 (study visit 15)** is conducted by the study nurse(s). The study form is filled in and blood donated according to flow chart. Abbreviated risk assessment and risk behaviour counselling are done.

**Week 64 (study visit 16)** is conducted by the study nurses(s)**.** Blood is donated for immunology.

**Week 72 (study visit 17)** is the final planned visit in the study. The visit is conducted by both the study nurse and the study doctor. Again the study doctor takes a complete medical history and performs a physical examination according to study visit 1. An extended risk assessment and risk behaviour counselling is performed and blood is donated according to flow chart. The visit should be recorded in the source documents including study number and any other information relevant to the study. All study subjects will be issued a card signed by the principal investigators (full names, tel. numbers and addresses) stating that the holder has participated as a volunteer in a HIV-1 immunization study and that the outcome of standard HIV diagnostic tests do not signify HIV-1 infection.

*2.4.1 Immunisations*

| **Group** | **N** | **Mode of Immunization**  **(w 0, 6 , 12)** | **Mode of delivery** | **Left arm (Ampoules 1**  **env)** | | **Right arm (Ampoules 2**  **gag, Rtmut)** | **Boost immunization**  **(w 36 and 60)** |
| --- | --- | --- | --- | --- | --- | --- | --- |
| B1 | 10 | Id  ZetaJet® | No electroporation | 1 inj 100µl  0,3 mg DNA* | 1 inj100µl  0,3 mg DNA* | | 1 im inj needle  MVA 108 pfu |
|  | 2 | Id  ZetaJet® | No electroporation | 1 inj 100µl saline | 1 inj 100µl saline | | 1 im inj needle  100µl saline |
| B2 | 10 | Id  ZetaJet® | electroporation | 1 inj 100µl  0,3 mg DNA* | 1 inj 100µl  0,3 mg DNA* | | 1 im inj needle  MVA 108 pfu |
|  | 2 | Id  ZetaJet® | electroporation | 1 inj 100µl saline | 1 inj 100µl saline | | 1 im inj needle  100µl saline |
| B3 | 10 | Id  ZetaJet® | electroporation | 1 inj 100µl  0,3 mg DNA* | 1 inj 100µl  0,3 mg DNA* | | 2 id inj Zetajet®,  tot. 0,6 mg DNA + electroporation |
|  | 2 | Id  ZetaJet® | electroporation | 1 inj100µl saline | 1 inj100µl saline | | 2 id inj Zetajet®,  tot 200µl saline +  electroporation |
| B4 | 10 | Id  ZetaJet® | electroporation | 1 inj100µl  0,3 mg DNA** mixed ampoules | 1 inj100µl  0,3 mg DNA** mixed ampoules | | 1 im inj needle  MVA 108 pfu |
|  | 2 | Id  ZetaJet® | electroporation | 1 inj100µl saline | 1 inj100µl saline | | 1 im inj needle  100µl saline |

*) 7 DNA plasmids **) 11 DNA plasmids.

Immunizations will be given as prime injections (HIV DNA) at weeks 0, 6 and 12 and as boost injections (MVA) at week 36 and week 60.

*2.4.2 Injections*

All **DNA** immunizations will be performed with a needle-free device, ZetaJet®, according to the manufacturer’s (Bioject Inc, Portland, Oregon) instruction.

Intradermal injections will be given over the deltoid muscle. Ampoule 1 will be given in the left arm and ampoule 2 in the right arm, except in the Group B4 where a mixture of vaccines from two identical ampoules will be given in both arms. Immediately after the injection subjects randomized to Groups B2, B3 and B4 will receive intradermal electroporation over the injection sites with the CytoPulse device, DermaVax, according to the manufacturer’s instruction.

All **MVA** injections will be performed with needle and syringe in the left deltoid muscle.

The site will be inspected after the immunisation, and any local reactions recorded on the case record form.

The immunisations will take place in an outpatient setting. Participants will be closely observed for 30 minutes after each immunisation, at which point vital signs (pulse, blood pressure and respiratory rate) will be recorded on the case record form, as well as any local or systemic reaction.

The needles, syringes and other materials will be disposed of according to local hospital regulations.

As with any parenteral vaccine, epinephrine and corticosteroids must be available for immediate use if an immediate hypersensitivity reaction, such as anaphylaxis, occur. Intravenous injections of vaccines will NOT be performed.

Study vaccine must not be administered to individuals with hypersensitivity to any component of the vaccine.

*2.4.3 Safety follow-up in the days following immunisation*

A diary card will be given, with instructions and a full verbal explanation, for participants to record local and systemic adverse events following immunisation, as well as medication taken. Volunteers will also be contacted the day following injection for a brief adverse reaction interview and subjects reporting any grade 2 or higher event will be prompted to a clinic visit. Should the volunteer be unreachable the designated contact will be contacted. In addition, volunteers will complete diaries over events for 7 days following each vaccination. Contact will be maintained by the clinical team, using a method chosen by the participant, as indicated by the evolution of adverse events, up to resolution of solicited local and systemic events. Additional visits may be recommended at the discretion of the clinical and principal investigators, if clinically indicated or in order to clarify observations.

All concomitant medication must be recorded in study form CRF with the reason for administration, the dosage regimen, the onset and end of treatment.

The following medications are prohibited while the subject is in the study:

- Immunomodulatory agents (i.e. immunoglobulin)

- Immunosuppressive agents (i.e., systemic steroids, chemotherapy)

- Live, attenuated vaccines. Other vaccines (subunit or killed) should be given at least two weeks before or two weeks after HIV immunization.

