Risks directly associated with injection in the skin is local pain. Pain caused by needlefree injection has previously been described as less than the discomfort caused by a conventional needle injection. Pain associated with electroporation in the skin is experienced as a shortlived pinch. The summarized discomfort associated with injections, electroporation and blood sampling is considered to be reasonable in proportion to the importance of HIV-vaccine development. Both needlefree injections and electroporation increase the uptake of DNA resulting in a relatively high concentration of DNA at the site of injection. It is theoretically possible that the local level of DNA increases the risk for integration at the site of injection. In previously performed studies the risk for integration is estimated to be lower than the frequency of spontaneous natural mutations in somatic cells. In this study it is an advantage that the skin is the target for electroporation and can easily be observed if any local disadvantages occur. We have performed preclinical tests for intergration with the plasmids to be used in this study in conjunction with electroporation and found no reason to suspect that integration will be a clinical problem. Punch-biopsies (3 mm) can be performed at different intervals – a procedure that is rutine in dermatological clinics and associated with a local discomfort at the level of blood sampling. The expected information gained is in reasonable proportion to planned actions. A possibility is that a slow decrease in the local level of DNA might improve the immunological effects of the vaccine. A consequence of the more effective immunization technique can be false positive reactions in routine serological diagnostic HIV-tests. All volonteers in this study will be offered access to additional assays that can distinguish the effects of immunization from those of HIV-infection as well as a certificate stating that this person is vaccinated with a vaccine causing immunological reactivites that might cause false postive reaction in conventional HIV-tests.

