**2.2 Screening**

The **first screening visit** (study visit 1) will take place between one to four weeks before visit two. At this visit the study subject will meet the study doctor(s) and study nurse(s) and the trial will be discussed in detail and an Informed consent for screening signed. The study doctor will take a complete medical history and perform a physical examination including mouth and throat inspection, palpation of lymph nodes, cardiac and pulmonary auscultation, abdominal palpation, blood pressure and body temperature. Medical status and medical history, including any ongoing medication and any previous allergic reactions, will be documented. These investigations can be postponed to the following visit. To ensure informed consent, subjects will go through the following process with a member of the study team and a more detailed check of eligibility conducted using a case record form and any questions about the study will be answered.

1. Pre-HIV test counselling
2. Safer sex counselling
3. That they should continue to use condoms with sexual partners whose HIV status is not known
4. The meaning of ‘randomisation’
5. The information will include potential adverse effects of the vaccine
6. Information about the fact that it is unknown whether or not the study vaccines will protect against HIV infection
7. Information that following immunisation they may develop antibodies that might produce a positive reaction in a routine HIV test, but that provisions have been made to distinguish between a post vaccination response and HIV infection during and after the trial
8. That participants probably will be excluded from donating blood or organs
9. That they may be subject to social risk if they develop HIV antibodies, or by revealing their participation in the study
10. The level of care that will be made available to them if they should be found to be HIV infected at any time during their participation in the study, including the screening period.

After signing written study consent the study subject is allowed to donate blood for safety laboratory tests including HIV antibody/antigen test. After a volunteer is found to be eligible, the screening number will become the study number. This means that study numbers may be discontinuous. The visit should be recorded in the source documents including conformity to inclusion and exclusion criteria, study number and any other information relevant to inclusion in the study.

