**6.1 HIV testing**

Only volunteers with a negative HIV antibody/antigen test result will be enrolled. A risk assessment will be undertaken prior to every immunisation and if risk status has changed then immunisation may have to be delayed until the HIV status of the participant is clarified. It is possible that participants may develop antibodies and test ‘positive’ in routine HIV ELISA assays subsequent to immunisation. The immunological and virological laboratories at SMI, will conduct additional tests to distinguish between infection and a post-immunisation response required either for clinical management, or at the request of a participant. The results from these tests will only be known to the study staff as positive or negative for HIV infection. At the end of the study specimens will be tested in real-time so that participants can be informed of the result and a plan to recall and retest them made should this be necessary. In the event of ongoing post-immunisation positive ELISA, the participants will be invited to re-attend annually until such time as this response has disappeared, and provided with an explanatory identity card in the interim.

*6.1.2 Verification of HIV status of participants*

If certification is required at the request of the participant, this can be provided by the trial team after testing at the local laboratory.

Results will always be given at an interview with a member of the study team unless the participant requests an independent physician, in which case this will be arranged.

If a specimen from a participant suggests that the participant is HIV infected, a second specimen will be collected and retested.

If a subject for any reason needs to establish his or her HIV status extended tests will be offered i.e. HIV RNA PCR or antigen test.

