**6.3 Social discrimination as a result of a post-vaccine response**

The aim is to minimise the possibility of social discrimination in participants who develop a positive HIV-ELISA test by providing HIV testing by PCR and certification for participants as required. In addition, an identification card stating that the individual has participated in a vaccine trial, with a contact number in case of medical emergency, will be provided.

In the unlikely event that a participant suffers social discrimination as a result of a post-vaccination response, the clinical investigators will assist the participant.

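### The week-72 card described in Protocol section 2.4 states without qualification that standard HIV test results do not signify infection, which is untrue of a holder who is or becomes infected

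*Protocol*

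**What the plan says.** At the final visit (Protocol section 2.4, Week 72, study visit 17) each participant receives a card signed by the principal investigators, with their names, telephone numbers and addresses. It records participation in "a HIV-1 immunization study and that the outcome of standard HIV diagnostic tests do not signify HIV-1 infection". The protocol reports the card's content and does not show its printed text.

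Other places deal with the same subject:

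- Introduction, Risk benefit analyses: volunteers are offered assays that separate the effects of immunisation from infection, and "a certificate stating that this person is vaccinated with a vaccine causing immunological reactivites that might cause false postive reaction in conventional HIV-tests".
- Section 2.2, item 7: volunteers are told that antibodies after immunisation might make a routine test positive, and that "provisions have been made to distinguish between a post vaccination response and HIV infection during and after the trial".
- Section 6.1: participants may test positive in routine ELISA. "In the event of ongoing post-immunisation positive ELISA, the participants will be invited to re-attend annually until such time as this response has disappeared"; they are also "provided with an explanatory identity card in the interim". The wording of that card is not given.
- Section 6.1.2: for anyone who needs to establish their status, "extended tests will be offered i.e. HIV RNA PCR or antigen test".
- Section 6.3: discrimination is to be limited by "providing HIV testing by PCR and certification for participants as required", and by "an identification card stating that the individual has participated in a vaccine trial, with a contact number in case of medical emergency".

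**The concern.** The card exists to stop a vaccine-induced antibody response being mistaken for infection, which is a proper aim. Its likely readers are clinicians outside the trial who do not have the protocol. As described, it tells them that a standard test result in this person does not signify infection. It does not say that the result may be misleading or that a further test is needed.

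The statement is made once, at the last visit, and has no expiry, so the holder can carry it for years. The low-risk commitment in the inclusion criteria (section 1.3.1) runs only for the duration of the study. If a holder is infected later and the card is believed, a true positive could be set aside, diagnosis delayed and partners exposed. A standard test is normally what prompts a PCR. A card that discounts the standard test without asking for the PCR weakens that step.

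**Working it through.** The protocol gives no figure on this point, so the check compares the texts.

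**1. Strength of the statement about infection**

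| Place in the protocol | Strength | Recipients and duration |
|---|---|---|
| Section 2.4, Week 72 card | Categorical: standard test outcomes do not signify infection | All subjects, no end date |
| Risk benefit analyses, certificate | Qualified: the vaccine *might* cause a false positive | All volunteers offered it |
| Section 2.2, item 7 | Qualified: *may* develop antibodies that *might* react | Everyone screened |
| Section 6.1, explanatory card | Surrounding text says *may*; card wording not given | Those with a persisting positive ELISA, in the interim |
| Section 6.3, identification card | No statement on what results mean | Participants; no limit stated |

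Only section 2.4 makes an unqualified statement about infection. Section 3.6 refers false-positive results to section 6, but nothing in section 6 withdraws or softens the section 2.4 clause.

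**2. Can the statement be untrue of a holder?**

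The protocol allows for it at two times.

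- *By week 72.* HIV infection is the first listed reason for stopping injections (section 3.7.1), and such subjects remain in the visit schedule. Section 6.2 sets out their care. An infected subject can therefore reach visit 17, where the card goes to everyone.
- *After week 72.* The card has no end date, and section 2.2 tells volunteers it is unknown whether the vaccines protect.

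In either case the literal statement is false for that person.

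**3. What the safeguards cover**

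- Infection by week 72: serology is done at the end of the study and suspect positives are verified by PCR (section 4.1.4). End-of-study specimens are tested in real time, with recall and retest if needed (section 6.1). A specimen suggesting infection leads to a second sample (section 6.1.2), and an infected participant is referred for specialist care and counselling (section 6.2). This period is largely covered.
- Infection after week 72: PCR or antigen testing is available (sections 6.1.2 and 6.3), and the investigators' contact details are on the card. Both depend mainly on someone contacting the team. Annual recall applies only to those whose vaccine-related ELISA reactivity persists.

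**4. Size**

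Four groups of 10 + 2 give 4 × 12 = 48 cards, for 4 × 10 = 40 vaccinees and 4 × 2 = 8 saline controls. The protocol gives no HIV incidence after the trial, no share tested elsewhere and no share of readers who would take the card literally. No harm rate can be calculated.

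**The case against.** The strongest reply is that section 2.4 paraphrases a card nobody has seen, in loosely written prose, and that the intent is plain from the rest of the protocol: a reactive routine test after vaccination is not in itself evidence of infection. The clause can also be read as saying that a standard result is not diagnostic in this person. That stays true even of an infected holder, because infection would be established by PCR or antigen test. Only standard tests are disclaimed. The remaining route to harm needs several events together, in volunteers selected for low risk and given extended risk counselling at that same visit.

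Much of this stands. The intent is probably benign, the milder reading is possible and the risk is small. But section 2.4 is the instruction for what the card will state, its readers will not have the protocol to supply the missing qualifier, and as described it does not ask for a confirmatory test.

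A reader might infer three stronger points that the documents do not support:

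- *That the protocol gives four conflicting versions of one card.* The risk-benefit text describes a certificate, section 6.1 gives no card wording, and section 6.3 is a short summary. All can stand beside a week-72 card. The difference shown is one of strength of statement.
- *That giving the card to the 8 of 48 controls (16.7%) is an error.* Vaccination cannot explain a reactive test in them, but clinic and laboratory are blinded to controls (Synopsis), so one card for everyone is needed. Nothing says that controls will not learn their allocation once the code is broken.
- *That a subject infected by week 72 would leave with only false reassurance.* Sections 4.1.4, 6.1 and 6.2 provide for testing, PCR verification and referral.

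**Conclusion.** The clause in section 2.4 is wrong as written, at low severity. Taken literally it is untrue of a holder who is or becomes infected, and it goes further than the protocol's own may/might wording in the risk-benefit text and in sections 2.2 and 6.1.

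The residual risk is small and cannot be quantified from the document. It lies mainly in infection after week 72, tested outside the trial, with the card taken literally and no confirmatory test or call made. The conclusion assumes that the printed card follows section 2.4; if the printed text already carries a qualifier, only the protocol sentence needs correcting. Endpoints, sample size and analysis are unaffected.

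**What to change.** Replace the one clause in section 2.4 with wording that holds for every subject and keeps the blind, for example:

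> *The holder took part in an HIV vaccine trial and may have received vaccine. A reactive standard HIV antibody test may be vaccine-induced and neither proves nor excludes infection; confirm by HIV RNA PCR or antigen test via the contact listed.*

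Check that the printed card says the same. This still protects participants from being mislabelled as infected. The cost is one sentence in the protocol and the matching card text. No test or visit is added, because confirmatory testing is already offered in sections 6.1.2 and 6.3.

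Aligning the certificate in the risk-benefit text and the cards in sections 6.1 and 6.3, and sending a notice to the controls after unblinding, are optional. Neither is needed to repair the error.
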